### Study partners

Three frontline harm reduction agency partners—Parkdale Queen West Community Health Centre (Queen West site), South Riverdale Community Health Centre, and The Works at Toronto Public Health—have been funded as DCS intake sites. With the exception of The Works, which is a public health agency, the remaining two partnering frontline agencies are community health centers, and all agencies combine harm reduction service delivery with access to other services, including primary care, mental health care, and social service programs. As DCS intake sites, agencies will collect drug samples from participants, administer intake and post-test surveys, facilitate transport of samples to clinical laboratories, and communicate analysis results to participants along with relevant harm reduction information. Notably, Parkdale Queen West Community Health Centre (Queen West site) also houses TRIP Project, a program providing information and resources on harm reduction and safer sex to youth in nightlife and party settings.

Clinical laboratory partners at the Centre for Addiction and Mental Health and St. Michael's Hospital—two urban hospitals with specialized programs for substance use—will analyze samples of drugs from participants at frontline harm reduction agencies using LC- and GC-MS techniques and guide the aggregation of analysis data across sites to identify composition (qualitative and quantitative) trends in the unregulated drug supply.

To bolster the relevance of findings and ensure effective knowledge translation strategies that address the needs of key populations, a Community Advisory Board made up of people who use drugs will advise on all aspects of the design, analysis, interpretation, and knowledge translation activities of this study [39]. Additionally, protocols for research methods and outcome measures will be aligned as much as possible with DCS implemented in other Canadian jurisdictions, including British Columbia and the capital city of Ottawa, Ontario, to maximize the potential comparability of findings across distinct settings.

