#### Estimated overdose incidence (Aim 3)

While no formal estimates of the overdose rate among people who use drugs in Toronto have been derived, 1002 overdose calls (fatal and non-fatal combined) were made to Toronto Paramedic Services between January 2018 and December 2018 in neighborhoods adjacent to the three frontline DCS sites, representing 31% of all calls across Toronto [49]; these neighborhoods are also those with the greatest density of people who use drugs [35]. We also note that the incidence of > 1000 overdose events recorded near DCS sites implies a relatively high event rate among potential DCS clients.

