#### Spatial patterns of fatal and non-fatal overdose in Toronto (Aim 3)

Employing approaches previously used to assess the association between risky drug-related behaviors and frontline services [55], data from the OCC and TPaS will be used to assess the spatial association between frontline harm reduction agencies with DCS and overdose events. This will be done by comparing geographic units that have DCS and SCS co-located with sites that only have SCS located, compared with sites that have neither. Changes over time in the incidence of overdose in these units will be determined by employing geographic information systems approaches. First, spatial buffers around each DCS site will be generated, and TPaS and OCC data will be used to capture the spatial location of non-fatal and fatal overdoses in surrounding areas. Significance testing will then be done by analyzing dissemination blocks (the smallest geographic unit defined by Statistics Canada with a population of 400–700 people). Toronto experienced 1542 non-fatal and 111 fatal overdoses over a recent 6-month period (August 2017–February 2018), and based on existing spatial data, it is estimated that the range of annual overdose events per dissemination block will range from 0 to > 100. This exploratory approach represents a simple descriptive test to determine the spatial correlation of overdoses and DCS. Second, to further account for potential confounding of the association between DCS and spatial patterns of overdose as a result of co-location of SCS and DCS [56], the mean distances between fatal overdoses (OCC data) in neighborhoods in which SCS are implemented but have not yet implemented DCS will be compared. Third, geographically weighted regression (GWR) will be employed to determine the spatial heterogeneity between the location of overdoses (dependent variable) and location of DCS (independent variable), while accounting for the presence of SCS as above. GWR calculates local spatial statistics by fitting a weighted regression equation for each dissemination block in the study area to assess local variation [57]. Local statistics will then be compared with the global statistic for the entire geographic area (i.e., the Province of Ontario), and blocks exhibiting local variation differing from the global statistic will be identified (including by undertaking a sub-analysis restricted to blocks within the City of Toronto). Using GWR, it will be determined whether those blocks exhibiting local variation in overdose incidence are more or less likely to also contain DCS. Fourth, the local annual incidence rate of overdose for each block will be determined. The Wilcoxon signed rank-test has previously been shown to be effective at assessing fluctuations in the annual rate of fatal and non-fatal overdose [56], and will allow a determination of slope differences in the overdose rate in blocks that do and do not have DCS.

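### Aim 3, fourth spatial step: a paired test is named for a comparison between two separate sets of blocks, so a shared trend could be read as a DCS effect

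*Protocol article*

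**What the plan says.** The section on spatial patterns of overdose (Aim 3) sets out four steps. It fixes the unit of analysis early: "Significance testing will then be done by analyzing dissemination blocks". The fourth step begins: "Fourth, the local annual incidence rate of overdose for each block will be determined". It then names the test and its justification: "The Wilcoxon signed rank-test has previously been shown to be effective at assessing fluctuations in the annual rate of fatal and non-fatal overdose". The same sentence ends by stating what the test will deliver: it "will allow a determination of slope differences in the overdose rate in blocks that do and do not have DCS".

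The section on study partners gives the number of exposed locations: "Three frontline harm reduction agency partners" that "have been funded as DCS intake sites". The spatial section opens with a three-way comparison (DCS and SCS together, SCS only, neither), and its first step draws buffers around the DCS sites. The fourth step names only two kinds of block. It does not say whether a block has DCS by containing a site or by lying within a buffer.

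The preceding section, on longitudinal analysis of overdose data (Aim 3), separately plans conditional fixed effects Poisson models. These compare relative change in incidence between areas with and without DCS, adjusting for SCS and for underlying trends.

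**The concern.** The justification offered is for a within-unit use, namely changes in the annual rate. The claim drawn from it is a between-group contrast, which is a different question. Blocks with and without DCS are separate and presumably very unequal in number, and the article does not pair them.

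A test of within-block change picks up whatever moves all blocks together. The Background section reports steep movement of that kind: opioid-related deaths in Toronto in 2017 were 125% above 2015. A significant signed-rank result in DCS blocks could therefore be reported as an effect of DCS when it reflects the city-wide course of the epidemic. A flat result could equally hide an effect that offset a rising trend.

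Table 1 lists spatial association with fatal overdose, and its change over time, as an Aim 3 outcome. This step's result would be read against that outcome.

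**Working it through.** The article gives no p-value, power or sample size for this step, so there is no figure of its own to reproduce.

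**Inputs from the article.** Test: Wilcoxon signed-rank. Unit: dissemination block. Data: annual rate per block. Claimed contrast: slopes in blocks with versus without DCS. DCS sites: three (study partners; estimated overdose incidence).

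**1. What the test can see.** For each unit the test takes one difference, d = after − before. It ranks the absolute values, sums the ranks of the positive differences, and asks whether the differences are centered on zero. Let T be the change shared by all blocks and E the extra change due to DCS. Non-DCS blocks then change by T and DCS blocks by T + E. The contrast wanted is (T + E) − T = E.

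- All blocks pooled: tests an overall change, mostly T.
- DCS blocks only: tests T + E = 0, which can fail through T alone.
- Each group tested separately: gives two p-values but no test of their difference, and the p-values depend on very different group sizes.
- DCS blocks matched to non-DCS blocks, differencing the changes: tests E = 0 and is valid, but no matching is described.

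**2. Smallest attainable p if the units are the blocks containing the sites.** With n non-zero differences all of one sign, the exact two-sided p is 2 × 0.5^n.

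| n | Smallest two-sided p |
|---|---|
| 3 | 0.25 |
| 4 | 0.125 |
| 5 | 0.0625 |
| 6 | 0.031 |
| 10 | 0.002 |

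Enumeration of all sign patterns agrees. Three sites give at most three such blocks, or three matched pairs, hence 0.25. Six pairs are needed to go below 0.05.

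**3. How far a shared trend misleads when there are more DCS blocks.** Simulation with 1,500 runs per setting and no DCS effect. Assumptions that do not come from the article: Poisson counts with mean 10 per block-year in both groups, and 200 comparison blocks. Entries are the share of runs with p < 0.05 for the before/after signed-rank test in DCS blocks.

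| DCS blocks | No trend | Common 20% fall | Common 25% rise |
|---|---|---|---|
| 3 | 0% | 0% | 0% |
| 6 | 2% | 6% | 9% |
| 15 | 6% | 39% | 47% |
| 30 | 6% | 69% | 76% |

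A two-sample rank-sum test on the block changes rejected in about 3% to 6% of runs throughout. More DCS blocks remove the floor in point 2 but make the confusion with trend worse.

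**4. What a two-sample test could reach with three DCS blocks.** With m comparison blocks the smallest two-sided rank-sum p is 2 / C(3 + m, 3).

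- m = 3: 2/20 = 0.10
- m = 4: 2/35 = 0.057
- m = 5: 2/56 = 0.036
- m = 10: 2/286 = 0.0070

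Five comparison blocks are enough to make p < 0.05 attainable.

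**The case against.** The strongest reply is that this is a condensed article and the full plan may pair the blocks. A signed-rank test on matched DCS and non-DCS differences would be a proper contrast, and how the cited source applied the test cannot be seen. This stands to a degree: the point is that the step does not work as worded, and not that a signed-rank test could never be used. But the article states what the test delivers, and without pairing that statement is wrong.

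Second, the consequence is limited. The Poisson models in the preceding section use the same coroner and paramedic data, adjust for trend and compare change between areas. The primary outcome is self-reported overdose in the participant survey (Aim 1). Both facts stand and lower the severity. The article's labels of exploratory and descriptive do not help here, because they follow the first spatial step and not the fourth.

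Third, some stronger conclusions that a reader might draw are not supported:

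- **That the step can never be significant.** The floor of 0.25 needs a DCS block to be one that contains a site. Exposure by buffer is an equally natural reading and would give more units.
- **That nearby blocks are coded as controls.** No such rule is stated for this step. The article places many overdose calls "in neighborhoods adjacent to the three frontline DCS sites", which says nothing about how individual blocks are classified.
- **That most block rates are zero.** Doubling the six-month count gives (1542 + 111) × 2 = 3306 events a year. If Toronto had 2.5 to 3.0 million people (an assumption), blocks of 400 to 700 people would number 2.5 million/700 = 3571 to 3.0 million/400 = 7500. The mean would be 0.44 to 0.93 events per block-year. At 0.93, a Poisson model gives exp(−0.93), about 40% zeros. The article itself expects 0 to more than 100 events per block, with clustering near the sites.

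**Conclusion.** The concern holds in a limited form. As worded, the fourth spatial step names a test that does not deliver the contrast claimed for it, because the signed-rank test has no between-group term and no pairing is described. This rests only on the article's wording and the definition of the test.

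The size of the problem depends on what counts as a DCS block. If it is a block containing one of the three sites, p cannot fall below 0.25. If it is any block in a buffer, a shared trend of 20% to 25% can produce rejection in roughly 40% to 75% of analyses with 15 to 30 blocks and no DCS effect. Those percentages depend on the assumed mean of 10 events per block-year.

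Severity is moderate. A reader might infer that Aim 3 has no valid test of the DCS effect on area incidence. The documents do not support that, because the Poisson models address it separately.

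**What to change.** Replace the signed-rank step with a between-group comparison of change, in one of two ways:

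- a two-sample rank-sum or permutation test on per-block changes or slopes, keeping the section's own three groups (DCS with SCS, SCS only, neither); or
- a group-by-period term in the Poisson model already planned in the preceding section.

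The Poisson term is the safer choice if baseline rates differ. A common 20% fall is 2 events on a baseline of 10 but 0.2 on a baseline of 1, so a rank test on absolute changes would again mix trend with effect; it should use relative changes. If buffers define exposure, blocks around the same site are not independent, and a permutation should reassign whole sites rather than single blocks.

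State whether a DCS block is one that contains a site or one within the planned buffer, and do not count blocks inside a DCS buffer as controls. The article does not give the number of SCS-only sites. If there are too few comparison units for p < 0.05 to be attainable, report the rate ratio and its interval as descriptive.

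The cost is a change of wording and a little programming. The data are already covered by the sharing agreements described under coroner and paramedic services. The resulting p-value may be larger.

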
### Mixed-methods analysis

A parallel mixed-methods design followed by a meta-inference process will be employed [58]. Specifically, qualitative research findings will be used to interpret survey- and laboratory-based data collection within the context of the lived experience of participants. This approach has been shown to be effective in generating an understanding of the social dimensions underpinning quantitative outcomes (e.g., use of and outcomes related to DCS, or the incidence and spatial patterns of overdose) [59–61]. Qualitative data collection and interpretation will also be used to refine the quantitative data collection process to better capture relevant factors.

### Ethics, consent, and permissions

Research Ethics Board approval has been obtained for this research study from Providence St. Joseph’s and St. Michael’s Healthcare, Toronto Public Health, Centre for Addiction and Mental Health, and University of Toronto. Client provision of informed consent is integrated into the baseline intake survey, although clients that are unwilling or unable to provide informed consent will still be provided access to DCS. Data will be securely stored at St. Michael’s Hospital.

## Results

The study addresses evidence gaps on the emerging continuum of responses to the opioid overdose crisis in Canada and elsewhere. Internationally, DCS have only targeted “recreational drug users,” and no DCS co-located with SCS and using LC- or GC-MS have been scientifically evaluated. The study therefore builds upon new and incremental lines of inquiry by evaluating the potential impact of DCS within a suite of harm reduction interventions tailored for populations at highest risk of overdose [62]. Given the rise in opioid overdose events and fatalities in Canada, the USA [63], and the UK [64], findings will provide decision makers with critical data on the potential impact of an innovative DCS model on overdose risk.

DCS in Toronto have been integrated within public health and community health agencies with existing SCS, thereby combining harm reduction service delivery with access to other services including primary care, mental health care, social service programs, and scientific evaluation. The implementation of DCS will allow frontline harm reduction agencies to extend their services by providing clients with timely information on the composition (qualitative and quantitative) of their drugs. While DCS are not a panacea for drug-related harms, increasing information on the unregulated drug supply may disrupt the risk environment for people who use drugs by equipping them with tailored and highly relevant information related to their substance use, as well as by increasing transparency and accountability in the drug market by reducing information asymmetries between buyers and sellers throughout the supply chain. Evidence from European DCS indicates that DCS benefits can extend beyond those individuals that engage directly with the service, as analysis results are often communicated to others, thus multiplying the preventive effect for a broader population of people who use drugs [65]. Although DCS can play an important role in drug market monitoring and therefore have the potential to influence drug market activities, the absence of legally regulated markets for illegal drugs creates a paradox wherein people who use drugs may become aware of dangerous adulterants in their drugs but have no viable option for the replacement of the analyzed substance. Particularly for those facing intersecting vulnerabilities such as poverty and substance-use disorders, increased information on substance composition may be insufficient to modify their risk environment. In cases where information from DCS does not effectively reduce overdose risk for clients, other policy approaches and interventions—such as scaling up low-barrier access to managed opioid programs—should be considered. Importantly, DCS have the potential to attract clients who may otherwise not access drug-related services—as has been demonstrated by DCS in Europe [18, 22, 66]—and given the co-location of DCS with other services, DCS may support increased uptake of other harm reduction, primary care, mental health care, and social services among people who use drugs. While such an integrated model of harm reduction services offers the promise of a “one-stop shop” with the potential to improve health outcomes for people who use drugs, drawbacks such as reduced anonymity may pose barriers for some clients. Accompanying evaluations of DCS and SCS will examine different models of service provision, under what conditions benefits can be maximized, suitability for specific subpopulations, and a variety of indicators including successful referrals to other services.

## Discussion

A crucial difference between the adoption of DCS in Toronto and the longstanding use of this harm reduction service throughout Europe is the targeted subpopulation of people who use drugs. Whereas most DCS globally target “recreational drug users,” in Toronto, DCS will primarily target marginalized people who use drugs accessing frontline services, many of whom use drugs regularly and by injection. This evolution in the application of DCS poses important questions that have not yet been explored, including optimal service delivery models and technologies, as well as unique barriers for this population. As the only DCS in Canada employing LC- and GC-MS analysis for point of care services, it will be important to compare results with DCS currently operating in British Columbia and Ottawa employing different and less sophisticated technologies (e.g., Fourier-transform infrared spectroscopy, fentanyl test strips), including in terms of the capability of technologies to detect drug market trends and respond to local drug use patterns. Although employing LC- and GC-MS for the analysis of drug samples has the potential to offer clients more information than the use of other technologies, the time required to receive analysis results may not be suitable for all populations of people who use drugs. It remains to be seen whether participants will consume their substance before receiving analysis results, and if they will modify their behaviors in response to analysis results, particularly when a high-potency opioid is detected.

### Limitations

The study has limitations typical of community-based intervention evaluations. Since denying access to DCS is not ethical or feasible, the recruitment process is being integrated directly into the delivery of DCS. While this will allow for the collection of data from a large proportion of the population of DCS clients, it does present limitations. For instance, it is not possible to estimate the number of individuals that will access DCS and provide data, nor the total person-time of data. Second, we note challenges in disentangling the impact of SCS and DCS on overdose incidence and related behaviors given that these two interventions will be co-located in our study setting. However, the 1-year delay between the implementation of SCS and that of DCS provides an ideal natural experiment to test the independent effects of these interventions. Further, the harmonization of data collection tools between SCS and DCS evaluations will further allow for the assessment of independent effects as we are able to evaluate outcomes among SCS clients who do and do not use DCS. Another limitation is the absence of a comparison group, except for the SCS sub-analysis. A final challenge worth noting is that while we would prefer that participants create an anonymous identifier, since this would allow us to link their data from separate visits to DCS and therefore employ panel approaches, this will depend upon the willingness of clients to consent to participating in the research, creating an anonymous identifier, and consistently recording their survey responses under their identifier at subsequent visits.

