#### Sample size (Aim 1)

In lieu of randomization, which is neither feasible nor ethical given the type of service to be examined in the present study, a community recruitment model will be employed whereby a survey of all consenting DCS clients is undertaken (i.e., the sampling frame consists of all clients of DCS). Since study participants are recruited “passively” through their use of the service, we are unable to estimate the proportion of surveys to be obtained from unique versus repeat clients until after DCS are implemented. We therefore cannot determine the total person-time data that will be collected. We note, however, that 75% of feasibility survey respondents recruited from frontline agencies reported being willing to access DCS. The total population of structurally vulnerable people who use drugs in Toronto is estimated at 9000, among whom 20% are willing to use SCS [35]; it is estimated that *n* = 1800 unique individuals who use drugs access frontline agencies. Previous literature suggests social desirability bias in reports of willingness to access harm reduction services [40]; we therefore estimate an approximate total of *n* = 1080 DCS clients.

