#### SCS client survey data (Aim 1 substudy)

An ongoing longitudinal cohort is collecting data from people who inject drugs who do and do not use SCS at the three frontline agencies participating in the DCS network. This allows for harmonization of survey tools across both projects. As such, for participants consenting to linkages, data from a standardized SCS cohort survey (e.g., age, gender, neighborhood of residence, and drug-using factors) and data from the SCS pre/post injection assessment form (e.g., overdose outcomes, whether emergency medical attention was provided [i.e., SCS staff response and/or call to 911 for paramedic response], naloxone administered) will be accessible for consenting participants. This will also allow for a substudy consisting of a comparison of outcomes (i.e., overdose incidence and related risk behaviors) among frontline agency clients who access SCS exclusively, who access both SCS and DCS, and who access neither.

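### Comparing SCS clients who do and do not choose DCS yields an adjusted association at best, not the independent effect claimed in the Limitations

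*Protocol article*

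**What the plan says.** The protocol article's section on SCS client survey data (Aim 1 substudy) describes the source: "An ongoing longitudinal cohort is collecting data from people who inject drugs who do and do not use SCS", drawn from the participating agencies. For clients who consent to linkage, it adds covariates from the cohort survey and "data from the SCS pre/post injection assessment form (e.g., overdose outcomes, whether emergency medical attention was provided". It then plans to compare overdose and risk-behaviour outcomes "among frontline agency clients who access SCS exclusively, who access both SCS and DCS, and who access neither". No time window, model or adjustment set is given for this comparison.

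Sample size (Aim 1) states that there is no randomisation and that "study participants are recruited “passively” through their use of the service".

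The Limitations first concede that SCS and DCS are hard to separate because they are co-located. They then say that harmonised data collection makes independent effects assessable, giving as the reason that "we are able to evaluate outcomes among SCS clients who do and do not use DCS". The next sentence makes this sub-analysis the study's only comparison group. Unknown client numbers and person-time, co-location and reliance on the anonymous identifier are listed as limitations. Self-selection into DCS is not.

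**The concern.** Within one agency, bringing a sample for checking is the client's own decision. It may follow a recent overdose or worry about the supply, or it may reflect general caution. Users and non-users can therefore differ in overdose risk before any sample is checked. Common questionnaires make the measurements comparable; they do not make the people comparable.

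The stakes are considerable because this is the only participant-level contrast with people who do not use DCS. Table 1 also lists self-reported overdose among those who do and do not access DCS as the first Aim 1 measure. If the difference is read as an effect of DCS, selection alone could produce an apparent benefit or an apparent harm.

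**Working it through.** The article states no overdose risk by DCS use, no size and no target effect for this substudy, so there is no figure of its own to reproduce. All risks and uptake figures below are assumptions that show how far selection alone can move the result.

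**1. Two-group illustration.** Let p1 be the 6-month overdose risk of DCS starters before DCS, and p0 that of SCS-only clients, stable over time. If DCS does nothing, the odds ratio seen afterwards is [p1/(1−p1)] / [p0/(1−p0)].

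- Starters at higher risk, 30% against 20%: 0.4286 / 0.25 = 1.71.
- The same groups with a true odds ratio of 0.70: 1.714 × 0.70 = 1.20, so a real benefit looks like harm.
- Starters more cautious, 15% against 20%: 0.1765 / 0.25 = 0.71, so a DCS with no effect looks like a 29% reduction in odds.

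**2. Selection through uptake, no true effect.** Let half of SCS clients be at high risk (pH) and half at low risk (pL = 10%), with DCS uptake uH and uL.

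- Risk in users = (uH·pH + uL·pL) / (uH + uL).
- Risk in non-users = [(1−uH)·pH + (1−uL)·pL] / [(1−uH) + (1−uL)].

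| pH | uH / uL | Users | Non-users | Odds ratio |
|---|---|---|---|---|
| 40% | 60% / 60% | 25.0% | 25.0% | 1.00 |
| 20% | 70% / 50% | 15.8% | 13.8% | 1.18 |
| 40% | 80% / 40% | 30.0% | 17.5% | 2.02 |
| 20% | 50% / 70% | 14.2% | 16.3% | 0.85 |
| 40% | 40% / 80% | 20.0% | 32.5% | 0.52 |

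The contrast is unbiased only when uptake does not depend on risk.

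**3. What differencing against a period before DCS would do.** With stable risks, the 1.71 from step 1 appears both before and after DCS starts, and 1.71 / 1.71 = 1.00, which is correct. Now suppose that the starters' 30% is a transient rise from 20%, that controls stay at 20%, and that DCS does nothing. The odds ratio is 1.71 before and 1.00 after, so the difference-in-differences odds ratio is 0.25 / 0.4286 = 0.58, a false benefit. The simple comparison afterwards would have been right.

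**4. Timing of the first overdose report.** Three places fix this.

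- Multivariable model (Aim 1): the outcome is overdose in the past 6 months.
- Intake and post-test surveys (Aim 1): the baseline intake survey is completed at the first DCS visit.
- Table 1: the intake survey is a source for self-reported overdose in people who do and do not access DCS.

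A client's first report therefore looks back over time that wholly precedes DCS use. Counted as an outcome among DCS users, it would attribute overdoses before DCS to people who had not yet used it.

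**5. Whether another analysis covers the gap.** The before-and-after contrasts under Aim 3 use areas, with coroner and paramedic data. The pre/post evaluation and the confounders in the Aim 1 model use DCS clients' own surveys. Neither is described as comparing individual DCS users with non-users on change from a value before DCS.

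**The case against.** The strongest reply has four parts.

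- **Independent means separate from SCS.** The sentence belongs to the discussion of co-location, and the Background frames the overall goal as an association. That is a fair reading, but it does not rescue the claim. Restricting to SCS clients fixes SCS access as yes or no; it does not fix intensity of SCS use or underlying overdose risk. The remaining difference is still not an effect of DCS.
- **The estimator may be in a fuller document.** This stands. A reader might infer that the comparison is restricted to data after DCS and ignores overdose data from before it. The article does not say so: it gives no window and rules nothing out. Nor does it state that such data exist for later DCS clients. That is a reasonable inference from an ongoing cohort, SCS forms that record overdose and a 1-year lead of SCS over DCS, but the cohort's start date is not given and linkage needs consent.
- **Some adjustment is provided for.** Linked demographic and drug-using factors would be available. Confounder adjustment, however, is described for the DCS survey models, not for this substudy.
- **Difference-in-differences has its own bias.** This also stands, as step 3 shows. It should not replace the comparison as the main analysis.

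**Conclusion.** The point holds as a matter of inference and timing. The Limitations attach effect language to a contrast between self-selected groups, and selection into DCS is not acknowledged. Under the assumed risks, a DCS with no effect shows an odds ratio of 1.71 or 0.71; across the uptake scenarios the range is 0.52 to 2.02. The sizes rest wholly on those assumptions and the direction of bias is unknown. That users and non-users may differ beforehand follows from the article's own definition of the groups.

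The documents do not support saying that the plan discards cohort data from before DCS, or that a difference-in-differences analysis must be primary.

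**What to change.** 1. Start follow-up at the first DCS visit for DCS users and at a matched calendar date at the same agency for SCS-only clients. Adjust for overdose history before that date, injecting frequency and SCS use, where the linked cohort or SCS records hold them.
2. Treat a DCS client's first-visit report of overdose in the past 6 months as a baseline value, not an outcome under DCS. Apply this also to the Table 1 measure of self-reported overdose in those who do and do not access DCS.
3. Report a within-person change contrast (difference-in-differences) as a sensitivity analysis, with more than one period before DCS where available, so that a transient rise ahead of uptake can be seen.
4. In the Limitations, replace the claim about independent effects with an adjusted association among SCS clients, and name self-selection into DCS as a limitation.

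The cost is analysis wording and date matching on linked records, as far as those records reach back before DCS. Clients without such a record drop out of the adjusted contrast, which costs some precision. Item 4 applies even if no earlier data prove to be available.
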